# Thrombectomy for Acute Ischemic Stroke With a New Device-Skyflow: Study Protocol for a Prospective, Multicenter, Stratified Randomized, Single-Blinded, Parallel, Positive Controlled, Non-inferiority Clinical Trial

**DOI:** 10.3389/fneur.2021.645431

**Published:** 2021-04-30

**Keywords:** skyflow, thrombectomy, acute ischemic stroke, large vessel occlusion, protocol

## Abstract

**Background:** Stent retriever thrombectomy is the standard treatment for acute ischemic stroke (AIS) with large vessel occlusion (LVO) in anterior circulation. The aim of the trial is to evaluate whether the new thrombectomy device-Skyflow can achieve the same safety and efficacy as Solitaire FR in the treatment.

**Method:** This study is a prospective, multicenter, stratified randomized, single blind, paralleled, positive controlled, non-inferiority clinical trial. The safety and efficacy of vascular recanalization in AIS patients who are treated with either a new thrombectomy device-Skyflow or with Solitaire FR and within 8 h of symptom onset will be compared. A total of 192 patients will be enrolled, each group with 96 patients. The primary endpoint is successful recanalization rate after the operation. The secondary efficacy endpoints are the time from artery puncture to successful recanalization (mTICI 2b-3), NIHSS scores of 24 h (18–36 h), and 7 ± 2 days after the operation, mRS scores, and the rate of patients with mRS 0–2 scores 90 ± 14 days after the operation, and the success rate of instrument operation. The safety endpoints are the rate of symptomatic intracranial hemorrhage (sICH) and subarachnoid hemorrhage at 24 h (18–36 h) post-operation, incidence of adverse events (AE) and serious adverse events (SAE), all-cause mortality, and incidence of device defects.

**Discussion:** This trial will provide information on the safety and efficacy of Sky-flow stent retriever in the treatment of AIS patients with anterior circulation LVO. The success of this trial will be the basis for the product to be finally officially listed and applied in China.

**Trial registration:** Registered on 11 March 2018 with Chinese clinical trial registry. Registration number is ChiCTR1800015166.

## Introduction

Stroke is one of the main causes of human disability and death. Acute ischemic stroke (AIS) accounts for about 80% of all types of stroke (1). The key to AIS treatment is to recanalize the occluded blood vessel as soon as possible and salvage the ischemic penumbra. Endovascular treatment (EVT) in patients with large vessel occlusion (LVO) has attracted much attention because of many advantages such as rapid recanalization, lower hemorrhagic transformation rate, and extended stroke interventional therapy time window (2–5).

The invention of the stent retriever is a huge advancement of EVT, which has been reported to achieve a higher recanalization and favorable clinical outcome rate (2). The stent retriever uses a temporary stent to capture the thrombus, and restore blood flow by squeezing the peripheral blood vessel wall and moving the thrombus. When the stent is withdrawn, the thrombus is captured in the stent gap and removed together with the stent. The food and drug administration (FDA) of USA approved Solitaire (Medtronic/ev3) and Trevo (Strike) stent retriever to be mainly used for the treatment of large vessel occlusive stroke in 2012. The Solitaire FR With the Intention for Thrombectomy (SWIFT) study (6) and Thrombectomy Revascularization of Large Vessel Occlusions in Acute Ischemic Stroke (TREVO 2) trial (7) declared that MT with the Solitaire FR stent (ev3 Covidien) and the Trevo stent (Stryker Neurovascular) achieved better revascularization than those with the Merci retriever device. And it is recommended to use the stent retriever for acute mechanical thrombectomy (MT) (Class I, Level A) in the treatment of acute anterior circulation LVO stroke in guidelines for the early management of patients with AIS (8).

At present, the China Food and Drug Administration (CFDA) has approved several thrombectomy devices of foreign companies to be listed domestically, including Solitaire FR (Medtronic/ev3), Trevo thrombectomy system (Stryker), and Revive self-expanding intracranial thrombectomy device (Codman). In recent studies, the new mechanical thrombectomy devices, such as EmboTrap, Tigertriever and NeVa^TM^, have also achieved a high recanalization rate and good clinical outcome (9–12). The safety and efficacy of the domestically-made mechanical thrombectomy devices, such as Tonbridge stent retriever, JRecan stent retriever, and Reco stent retriever, have been verified in animal experiments or clinical trials, but they have not yet been widely used (13–15). In China, stent retrievers are still mainly imported and are expensive, making a lot of patients unable to receive effective treatment.

In order to better meet the domestic AIS patients and the ever-increasing clinical needs, Skynor medical (Shanghai) co. LTD designed a new thrombectomy device-Skyflow which has been approved by CFDA. The thrombectomy device is mainly composed of stent retriever and an introducer sheath, and the stent retriever including a stent and a pushing wire. There are marks of platinum alloy on the stent, which can be seen through DSA or X-ray. The stent can be released and retrieved by pushing and pulling the delivery wire. And the stent retriever is compressed into an introducer sheath, which is designed to facilitate stent loading into the microcatheter. The length of the delivery wire of the device is 185 cm, and the inner diameter of the compatible micro catheter is 0.021″/0.027″. It is divided into different specifications according to stent diameter of 3, 4, or 6 mm (Figure 1).

**Figure 1 F1:**

Description of stent composition: there are different sizes of stent retriever, including TD 320, TD420, TD430, and TD440 requiring a compatible microcatheter of 0.021 inch and TD620 and TD630 requiring a compatible microcatheter of 0.027 inch. Stent retriever with double helix structure, partial large mesh and full development design (1), pushing wire 185 cm with a variable-diameter structure coiled with platinum alloy coil in the distal (2), introducer sheath (3), diameter of stent, 3 mm for TD 320, 4 mm for TD420, TD430, and TD440, 6 mm for TD620 and TD630 (D), and stent retriever effective length, 20 mm for TD 320, TD420, and TD620, 30 mm for TD430 and TD630, and 40 mm for TD440 (L).

This clinical trial aims to evaluate the safety and efficacy of the new thrombectomy device-Skyflow for patients of AIS with large vessel occlusion in anterior, and provide a basis for the product to be finally officially listed and applied.

## Method

### Objective

The aim of the trial is to evaluate the safety and efficacy of the new thrombectomy device-Skyflow in the treatment of AIS to provide a basis for product registration, listing, and application.

1 *blood routine test: Hgb, Hemoglobin Content; RBC, Red Blood Cells Count; WBC, White Blood Cell Count; NEUT, Absolute Neutrophil Count; NEUT%, neutrophil ratio; PLT, Platelet Count*;

2 *routine coagulation test: PT, Prothrombin Time; APTT, Activated Partial Thromboplastin Time; INR, the international normalized ratio*;

3 *liver function test: AST, aspartate transaminase; ALT, alanine transaminase; STB, serum total bilirubin; TP, Serum Total Protein; ALB, serum albumin*;

4 *renal function test: Scr, serum creatinine; BUN, Blood Urea Nitrogen*;

5 *pregnancy test: blood HCG or urine pregnant test, Suitable for women of childbearing age*;

6 *brain CT or MR: identify whether there is intracranial hemorrhage, massive cerebral infarction or angiemphraxis before the interventional procedure, and whether there is intracranial hemorrhage after procedure*;

7 *cerebrovascular DSA: identify whether there is initial carotid artery occlusion, carotid artery dissection or arteritis, whether there is a tortuous vessel path that makes it difficult for the test/control device to reach the target position, the target vessel and the diseased segment, the proximal diameter of the occluded vessel, mTICI before, and after the operation*;

8 *record the use of anticoagulant, antiplatelet drugs, and drug for adverse events*.

### Participants

#### Inclusion Criteria

Patients eligible for inclusion will meet the following criteria (6, 16, 17):

Aged 18–80 years, clinical signs consistent with AIS.Clinical signs consistent with AIS; Subjects who are able to be treated within 8 h of onset of stroke symptoms; NIHSS ≥ 6 and <30 at the time of randomization.Occlusion in the intracranial internal carotid, or M1/M2 segment of the middle cerebral artery (MCA) confirmed by DSA.Prestroke Modified Rankin Score ≤ 2.Informed consent of the patient or family member.

#### Exclusion Criteria

Patients will be excluded if they meet any of the following criteria:

CT or MRI evidence of hemorrhage or infarction involving greater than 1/3 of the MCA territory (or in other territories, > 70 ml of tissue on presentation, or CT/DWI-ASPECT <6).Bilateral internal carotid artery occlusion detected by DSA.Initial segment of internal carotid artery occlusion or carotid artery dissection detected by DSA.The route artery is too tortuous for test/control equipment to reach the target position.Severe and sustained hypertension (defined as systolic blood pressure >185 mmHg or diastolic blood pressure >110 mm Hg under the treatment of antihypertensive drug).Baseline platelet count <40 ×10^*^9/L or recent oral anticoagulant therapy with INR>3.Baseline blood glucose <2.8 mmol/L or > 22.20 mmol/L.Having a heart, lung, liver, and kidney function failure or other serious diseases, such as intracranial malignant tumors, intracranial arteriovenous malformation, arteritis, systemic infection, and activity of disseminated intravascular coagulation, with serious disabling stroke within 6 months and severe mental illness.Can't cooperate with interventional surgery or can't tolerate.Life expectancy of less than 90 days.Known serious sensitivity to radiographic contrast agents.Female who is pregnant or lactating or has a positive pregnancy test at time of admission.Involved in other drugs or equipment trials within 3 months before randomization.

### Criteria and Procedures for Discontinuing Trial/Trial Treatment

#### Dropout Criteria

All subjects who sign an informed consent form and are selected to be enrolled in the central randomization system are entitled to withdraw from the clinical trial at any time. As long as they didn't complete the clinical trial observation, it should be considered as dropout cases.

#### Management of Dropout Cases

When a subject drops out, the researcher must fill in the reason in the CRF, and contact the subject as much as possible to complete the assessment items and record the last follow-up time. The CRF should be reserved for future reference. For cases who drop out due to adverse events, in addition to being recorded in the CRF, they should be also included in the adverse event evaluation. The random number of dropout cases cannot be replaced.

#### Elimination Criteria

Subjects who meet one of the following criteria should be eliminated: being falsely enrolled or neither using test devices nor control devices.

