#### Management of Eliminated Cases

The researcher must fill in the elimination reason in the CRF and the CRF should be reserved for future reference. The random number of eliminated cases cannot be replaced.

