### Endpoint Measurement

The primary endpoint is successful recanalization rate. It is defined as the proportion of target vessels achieving successful recanalization [modified Thrombolysis in Cerebral Infarction (mTICI) 2b-3].

The secondary efficacy endpoints are the times from artery puncture to successful recanalization (mTICI 2b-3), NIHSS scores 7 ± 2days after the operation, mRS scores and the rate of patients with 0–2 scores 90 ± 14 days after the operation, and the success rate of instrument operation (the rate of instruments being successfully delivered, released, and withdrawn in this group).

The safety endpoints are the rate of symptomatic intracranial hemorrhage (sICH) and subarachnoid hemorrhage at 24 h (18–36 h) post-operation, incidence of adverse events (AE) and serious adverse events (SAE), all-cause mortality and device defects.

sICH is defined as any ICH associated with neurological deterioration assessed by 4 or more points increase on the NIHSS score within 18–36 h. Adverse events are unfavorable medical events that occur during clinical trials, whether related to the test device or not, including hematoma or hemorrhage at the site of puncture, air embolism, infection, distal embolization, vascular spasm, thrombosis, vascular dissection and perforation, embolism, acute occlusion, ischemia, intracranial hemorrhage, pseudoaneurysm formation, neurological deficits including stroke, and death, and device deformation, fracture and malfunction. Serious adverse events are defined as any events which can cause deaths or serious health deterioration that occur during clinical trials, including fatal diseases or injuries, permanent defects of body structure or function, events that need hospitalization or can prolonged hospitalization, events that need medical or surgical intervention in order to avoid permanent defects in body structure or function, and events that can cause fetal distress, fetal death, or congenital anomalies and congenital defects. Device defects refer to the unreasonable risks of medical devices under normal use that may endanger human health and life safety during the clinical trials, such as incorrect identification and device breakage.

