### Randomization

Immediately after DSA and prior to mechanical thrombectomy, 192 patients are randomly allocated in a one-to-one ratio to either experimental or control group using an Internet-based Central Random System (IWRS). When grouping the patients, stratification will be performed to control key indicators by the clinical trial center and the baseline NIHSS score (divided by NIHSS score ≤ 17 points or > 17 points) (2).

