### Statistical Analysis

For descriptive analysis, enumeration data will be expressed by frequency and composition ratio, and the measurement data will be expressed by the mean, standard deviation, maximum, minimum, median, 25th and 75th quantile.

For baseline demographics, all date will be analyzed based on full analysis set. Continuous calibration Chi-square tests or Fisher's exact tests will be used for comparison of enumeration data between groups. Group *t-*test will be used for comparison of normally distributed measurement data between groups, and Wilcoxon Rank Sum test for non-normally distributed measurement data.

For the primary outcome, the successful recanalization rate of blood vessels, the CMH chi-square analysis with adjusted center effect will be used for comparison between groups based on full analysis set and per protocol set. In addition to the success rate, the difference in the success rate between the experimental group and the control group and the 95% confidence interval with the lower bound greater than −12.5% will be also estimated.

Other efficacy indicators comparation between groups will be the same as the baseline analysis. The paired *t-*test will be used for the intra-group comparison of normally distributed measurement data and the Wilcoxon Sign Rank test for the intra-group comparison of non-normally distributed measurement data.

For safety evaluation, the number and proportion will be used to describe cases that were normal before treatment and abnormal after treatment in the full analysis set. Adverse events will be described by number and incidence, and this incidence will be tested by continuous calibration Chi-square tests or Fisher's exact tests. At the same time, the specific manifestations and extent of all adverse events in each group and their relationship with the research products will be described in detail.

For missing data, only the missing primary endpoint indicators will be carried forward during analysis, while other indicators will be not. Incorrect and unreasonable data will be checked by the electronic data capture (Electronic Data Capture, EDC) system and the question will be answered by the researcher before statistical analysis. For patients withdrawing from the trial, the information will still be included in the final statistical analysis.

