## Discussion

Stent retriever has recently been widely used for thrombectomy, and has been reported to be associated with faster reperfusion and higher rate of successful recanalization in endovascular treatment of intracranial LVO (19). However, the research and development of domestic stent retrievers is relatively slow and few devices have been verified by clinical trials (15), which greatly hinders the progress of endovascular treatment in China. The purpose of this trial is to verify whether the new thrombectomy device-Skyflow has similar safety and efficacy compared with Solitaire FR in the treatment of acute LVO.

Compared with other stent retriever, the device-Skyflow has some unique structural features (15, 20, 21). The double helix structure makes stent have excellent flexibility and adhesion, which improve the thrombus removal rate, while avoid excessive damage for intracranial blood vessels. Partial large mesh design and the wall thickness greater than the rod width can effectively embed and remove the thrombus. Full development design helps the doctor to determine the position and length of the stent and its unfolding shape which can improve the success rate of the operation. The pushing wire of the thrombectomy device is made of nickel-titanium material, and the distal end is designed as a variable-diameter structure coiled with platinum alloy coil, which improves the pushability and visualization of the product. And the device has different models and specifications, which can meet the requirements of occluded vessel with different diameters. All these features provide theoretical basis for the safety and efficacy of the test product. But relative to the reel overlap design and multi-target combination with thrombus of solitaire FR, the Skyflow has a weaker cutting and grasping ability for thrombus. In addition, compared to solitaire FR, the delivering catheter of Skyflow device is larger, which may make it difficult to pass the Atherosclerotic stenosis.

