The Solitaire FR is a representative of stent retriever and the technology is mature. The main structure, action principle, treatment method, indications, etc. are similar to the test product (20). Therefore, it is reasonable to choose Solitaire FR device as a control product in our trial. In addition, this trial has strict inclusion and exclusion criteria. DSA is used to identify the occlusion site, and CT or MRI to exclude patients with preoperative intracranial hemorrhage and large core infarct. And the trial adopted a stratified random approach to avoid the influence on the results of preoperative NIHSS score and different research centers. A series of other measures have also been taken to ensure the quality of research, including the supervision of the experimental equipment of clinical trial institutions and relevant training for the investigators, quality control and monitoring, and data management and check after the research etc. These can make the trial results more convincing. But this is a single-blind clinical trial. The researchers cannot be blinded due to the difference of appearance between the test device and the control device, which can cause an impact on the trial results.

In conclusion, results of this trial will provide information on the safety and efficacy of Skyflow stent retriever. The success of this trial will provide a new option for the treatment for patients of AIS with LVO in China.

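### Randomised patients can be eliminated on post-randomisation grounds by unblinded staff, and the article does not confine this to the per-protocol set

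*Protocol article*

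**What the plan says.** Elimination Criteria gives two grounds for eliminating a subject: "being falsely enrolled or neither using test devices nor control devices". Management of Eliminated Cases requires a recorded reason and a retained case report form, and adds: "The random number of eliminated cases cannot be replaced". Eliminated subjects are therefore already randomised.

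Randomization fixes the timing: "Immediately after DSA and prior to mechanical thrombectomy, 192 patients are randomly allocated in a one-to-one ratio". The Discussion concedes that "The researchers cannot be blinded due to the difference of appearance between the test device and the control device".

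Statistical Analysis says that the method for the primary endpoint "will be used for comparison between groups based on full analysis set and per protocol set". Safety is analysed in the full analysis set. Neither set is linked to elimination. Withdrawn patients are expressly kept in the final analysis, and Management of Dropout Cases keeps those who leave because of adverse events in the adverse event evaluation. Nothing comparable is said of eliminated cases.

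Three other places bear on the point:
- One exclusion criterion reads "The route artery is too tortuous for test/control equipment to reach the target position".
- Endpoint Measurement makes device delivery a secondary outcome: "the rate of instruments being successfully delivered, released, and withdrawn in this group".
- The Discussion says of the test device that "the delivering catheter of Skyflow device is larger, which may make it difficult to pass the Atherosclerotic stenosis".

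**The concern.** Whether a study device is used is settled after allocation, by someone who knows the arm. False enrolment is also open-ended: nothing confines it to eligibility facts established before randomisation, and no masked decision is described. By contrast, the core laboratory overrides the clinician on recanalisation.

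A patient in whom the procedure is abandoned, or who is later declared ineligible after a difficult delivery, is unlikely to be a recanalisation success by the assigned device. Removing such patients takes failures out of the denominator. If it happens more often in one arm, the observed difference shifts in that arm's favour. In a non-inferiority trial a shift towards the test device increases the risk of accepting a device that is worse by the full margin. The per-protocol comparison is exposed in any case. The full analysis set, and with it the safety analysis, is exposed if elimination reaches that far.

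**Working it through.** **Inputs.** From Sample Size: 90% success in both arms, margin 12.5 points, 5% two-sided significance, 80% power, 5% dropout, 96 per arm. From Statistical Analysis: non-inferiority if the lower 95% limit of the difference exceeds −12.5%. Assumed: an unadjusted Wald interval, and the fraction eliminated, for which the documents give no figure.

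**Step 1, the plan's own N.** n per arm = (1.960 + 0.842)² × (0.9×0.1 + 0.9×0.1) / 0.125² = 90.4, so 91. Then 91/0.95 = 95.8, so 96 per arm and 192 in total. The stated size reproduces.

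**Step 2, how few patients matter.** Lower limit = d − 1.96 × √[p_T(1−p_T)/n_T + p_C(1−p_C)/n_C], with control fixed at 86/96.

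| Test arm, all randomised | Lower limit | After removing failures | Lower limit |
|---|---|---|---|
| 82/96 | −13.5% (fails) | 1 removed: 82/95 | −12.49% (passes) |
| 81/96 | −14.7% (fails) | 3 removed: 81/93 | −11.6% (passes) |
| 79/96 | −17.1% (fails) | 5 removed: 79/91 | −12.0% (passes) |

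First row: d = 82/96 − 86/96 = −0.0417 with standard error 0.0476; after removal, d = −0.0327 with standard error 0.0471. Five patients is about what the 5% allowance covers (96 × 0.05 = 4.8).

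**Step 3, false non-inferiority rate.** Set the true all-randomised rates at the margin, 77.5% versus 90%. In each arm a fraction e are failures that are eliminated, so the success rate among those left is p/(1−e). For example, 0.775/0.95 = 81.6%. The number eliminated is binomial (96, e), successes among the rest are binomial, and the chance of passing the rule is summed exactly.

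| Eliminated, test | Eliminated, control | Apparent rates | False non-inferiority |
|---|---|---|---|
| 0% | 0% | 77.5% v 90.0% | 2.8% |
| 1% | 0% | 78.3% v 90.0% | 4.0% |
| 2% | 0% | 79.1% v 90.0% | 5.6% |
| 3% | 0% | 79.9% v 90.0% | 7.6% |
| 5% | 0% | 81.6% v 90.0% | 13.7% |
| 8% | 0% | 84.2% v 90.0% | 29.4% |
| 5% | 2% | 81.6% v 91.8% | 7.6% |
| 5% | 5% | 81.6% v 94.7% | 2.4% |

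The 2.8% in the first row against a nominal 2.5% belongs to the Wald interval, not to elimination.

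**Step 4, power if everyone is kept.** At 90% in both arms and 96 per arm, power = Φ(0.125/√(2×0.09/96) − 1.96) = Φ(2.887 − 1.960) = 82%.

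**The case against.** Much of the case against a stronger claim stands.

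- **The full analysis set and safety.** A reader might infer that the full analysis set departs from intention to treat and that harms in eliminated patients are lost. The article says neither. It names no analysis set when it speaks of elimination, and the definitions may sit in a full protocol or SAP that is not shown. The point is only that the wording permits this.
- **Failed delivery as non-use.** A reader might infer that a device that fails to reach the clot counts as not used. A device opened and attempted is more naturally a used one, and delivery failure is part of the instrument-operation endpoint. The non-use ground covers mainly abandoned procedures; a failed delivery would leave chiefly as false enrolment.
- **The tortuosity route.** Table 1's note on DSA places the tortuosity judgement at angiography, and randomisation follows angiography. Relabelling a failed delivery afterwards would misapply the protocol. The text does not direct it, but neither does it rule it out.
- **Difference between arms.** The elimination rule and the tortuosity criterion cover both devices. The Discussion's remark concerns stenosis, not tortuosity, and says only that passage may be difficult. It makes a delivery disadvantage plausible and does not prove it. With equal elimination there is no inflation.
- **Audit.** Reasons are recorded, numbers are not replaced and all adverse events must be recorded, so eliminations can be traced. That helps a later reader but does not settle who is in the primary analysis.

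What the objection does not remove is that a rule is written down. It acts on randomised patients, one ground is a post-randomisation event, the other has no time limit, and the people deciding can know the arm. A SAP that followed this text would carry the same weakness.

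**Conclusion.** The point holds as a defect in a stated rule, not as evidence that test-arm failures will be removed. The per-protocol comparison is affected at the least; removal from the full analysis set is left open. The size depends on an elimination rate that the documents do not give and on its difference between arms. At true rates on the margin, test-arm-only elimination of 2% to 5% (about 2 to 5 of 96 patients) takes the false non-inferiority rate from about 2.8% to between 5.6% and 13.7%, and 5% versus 2% gives 7.6%. These figures assume that every eliminated patient is a failure and that the interval is an unadjusted Wald interval. Near the margin a single eliminated patient can reverse the conclusion.

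**What to change.** State in the elimination section and in Statistical Analysis that:

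1. All randomised patients stay in the full analysis set in the assigned arm. For the primary non-inferiority analysis, a device not delivered or not used after randomisation counts as not successfully recanalised.
2. An attempted but undelivered device counts as an instrument-operation failure.
3. Elimination affects only the per-protocol set. False enrolment means an eligibility violation shown by pre-randomisation data, decided masked to arm and outcome before database lock.
4. Safety is reported for all randomised patients in whom the procedure was started.

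The first item attaches an explicit failure rule to an endpoint now defined only by the mTICI grade, so it should be written as part of the primary analysis.

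The cost is wording, with slightly lower success rates in both arms. N stays at 192, with about 82% power if the planned 90% already describes all randomised patients. If counting non-delivery lowered both arms by a relative 2%, to 0.90 × 0.98 = 88.2%, the Step 4 formula gives Φ(0.125/√(2×0.882×0.118/96) − 1.96), about 77%. If only the test arm fell to 88.2%, power would be about 66%, but that would reflect a real device difference that the trial is meant to detect.
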